#### Qualitative data

Qualitative data will be assessed with respect to the feasibility, need, and acceptance of the on-site intervention and the digital support intervention (*t*_2_, *t*_4_) with semi-structured qualitative interviews. The structure and themes will be based on previous research [63] and adapted to the current pilot study. Participants will also be asked for their reasons for choosing their respective group. The qualitative interviews will be conducted and recorded via WebEx by Cisco and transcribed verbatim by trained students. Recordings will be used exclusively for scientific evaluation and will be deleted after they are transcribed.

### Statistical analysis

We plan to form two groups of 15 participants each. This compromises between the recommendation for both sample sizes for pilot studies [28] as well as group sizes for group interventions in RCTs [9]. Data will be analyzed within the framework of a mixed-methods approach with a parallel design with the IBM Statistical Package for the Social Sciences (SPSS) software, version 29. Results from the quantitative and qualitative data analyses will be compared accordingly. Quantitative and qualitative findings will be integrated at the interpretation stage.

#### Descriptive statistics

To describe the study population, means or medians and standard deviations will be calculated for metric variables. Frequencies and proportions will be calculated for categorical variables.

#### Inferential statistics

Multivariate analyses (e.g., mixed ANOVAs) will be applied to estimate the effect size of the planned primary outcome for the RCT (BSFC-s). This estimate will inform the case numbers calculation for the following RCT, while accounting for an overestimation due to the small sample size [38]. Additionally, pre–post changes, group effects and group-by-time interactions will be explored using effect sizes and confidence intervals. A responder analysis will be conducted to determine which CGs benefit the most from the interventions.

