**Methods:**

The non-randomized, prospective pilot study will be performed on-site in Oberstdorf, Bavaria (Germany) and online from April 2026 to January 2027. Working CGs with a moderate CG burden caring for a CR with a moderate need for assistance will be included. The intervention will be developed in participation with CGs and experts in the corresponding field. Two groups (A and B) will participate in the same on-site treatment but will differ in the intensity of the digital support phase (A: low; B: high) and the location of the refresher treatment (A: on-site; B: digital). Within the framework of a mixed-methods design, quantitative and qualitative data will be collected: the main outcome will be CGs’ satisfaction with the outpatient preventive medical service, assessed with the Client Satisfaction Questionnaire and qualitative interviews. For secondary outcomes, several aspects of the CGs’ mental and physical health will be assessed via questionnaires and qualitative interviews. Quantitative data will be analyzed descriptively and explored with MANOVA; qualitative data will be examined with content analysis.

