#### Secondary outcome measures

For secondary outcomes, we will assess sum scores at baseline, after each part of the intervention, and at follow-up (*t*_1_, *t*_2_, *t*_3_, *t*_4_, *t*_5_), and we will explore the change in sum scores for the following instruments:*Perceived Stress Scale-10* [16], German version [33]. This instrument includes the scales helplessness (6 items, score 6–30), self-efficacy (4 items, score 4–20), and overall perceived stress on a 5-point Likert scale ranging from 1 (never) to 5 (very often). The total sum score ranges from 10 to 50, with higher scores indicating more perceived stress.*Patient Health Questionnaire-9* (PHQ-9; [36]), German version [26]. This instrument measures depression severity with 9 items rated on a 4-point Likert scale ranging from 0 (not at all) to 3 (nearly every day). The sum score ranges from 0 to 27, with higher scores indicating more severe depressive symptoms [36].*Patient Health Questionnaire-15* (PHQ-15; [37]), German version [26]. This instrument captures psychosomatic complaints with 15 items rated on a 3-point Likert scale ranging from 0 (not bothered at all) to 2 (bothered a lot). The sum score ranges from 0 to 30, with higher scores indicating more severe symptoms [37].*Burden Scale for Family CGs-short form* (BSFC-s; [25]), German version. This instrument captures CGs’ subjective burden with 10 items rated on a 4-point Likert scale ranging from 0 (strongly disagree) to 3 (strongly agree). The sum score ranges from 0 to 30 with higher scores indicating higher subjective burden.*Maslach Burnout Inventory* (MBI; [42]), German version [13]. This instrument contains 22 items rated on a 7-point Likert scale ranging from 0 (never) to 6 (every day). It captures Emotional Exhaustion (9 items, with the sum score ranging from 0 to 63 such that higher scores indicate greater feelings of exhaustion), Depersonalization (5 items, with the sum score ranging from 0 to 45, such that higher scores indicate greater feelings of depersonalization), and Personal Accomplishment (8 items, with the sum score ranging from 0 to 72, such that higher scores indicate greater feelings of competence).*Three-item Loneliness Scale* (TILS; [30]), German version. This instrument measures participants’ loneliness with 3 items rated on a 3-point Likert scale ranging from 1 (hardly ever) to 3 (often). The sum score ranges from 1 to 9. Scores ranging from 3 to 5 indicate no loneliness, whereas scores ranging from 6 to 9 indicate loneliness.

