#### Progression criteria

Thresholds for feasibility (recruitment rate, retention rate, and adherence rate) and satisfaction, informing the decision to proceed to an RCT (“Go”) or otherwise to amend the study design [44] were established (see Table 1). Threshold values for recruitment rate [20], retention rate [56, 57], adherence rate [57, 72], and satisfaction [57] were derived from comparable projects addressing the same target population of CGs. Thresholds were set conservatively to account for the anticipated recruitment challenges [9], the duration of the project, and the high probability of change in the informal care arrangement over the course of the study, which would result in participant exclusion.

**Table 1 Tab1:** Progression criteria with benchmarks

Domain	Metric	Go
Recruitment rate	Proportion of eligible CGs consenting to participate	≥ 65%
Retention rate	Proportion of CGs completing the *t*_5_ follow-up data collection	≥ 60%
Adherence rate	Proportion of sessions attended (on-site and digital)	≥ 80%
Satisfaction	Proportion of CGs with a sum score ≥ 23 on the primary outcome measure (ZUF-8), averaged across all data collection time points	≥ 75%

*Note*: *CG* caregiver, *ZUF-8* German version of the Client Satisfaction Questionnaire

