While this pilot has some anticipated difficulties, it also has strengths. First, due to the participatory nature of the development of the outpatient preventive medical service, we can respond specifically to the CGs’ needs. Thus, we can develop a treatment program that is both helpful and realistic. Second, as data will be collected via phone, we expect little missing data. Third, by collecting data over a period of 9 months, we can examine the long-term development of the CGs. Fourth, due to the mixed-methods approach, we expect a comprehensive data collection that allows quantitative results to be explained and expanded by qualitative data. Fifth, with the overall results, we can further adapt the program to the participating CGs’ perspectives and experiences.

The information and knowledge gained from the pilot study, which will focus primarily on feasibility and satisfaction, will be used to plan an RCT that will focus on the sustainable implementation of the developed outpatient preventive medical service.

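### The models named for the BSFC-s (mixed ANOVA, MANOVA) in their standard SPSS form keep only CGs with every visit, and a five-visit group main effect would average in two visits before A and B differ

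*Protocol article*

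**What the plan says.** - **Model.** Inferential statistics: "Multivariate analyses (e.g., mixed ANOVAs) will be applied to estimate the effect size of the planned primary outcome for the RCT (BSFC-s"). The resulting estimate is to inform the RCT sample size, with an allowance for overestimation from the small sample. The Methods part of the abstract says: "Quantitative data will be analyzed descriptively and explored with MANOVA". The software is SPSS 29.
- **Effects.** Besides pre-post changes, "group effects and group-by-time interactions will be explored using effect sizes and confidence intervals".
- **Visits.** For the BSFC-s and the main secondary scales, "we will assess sum scores at baseline, after each part of the intervention, and at follow-up", that is t1 to t5. BBCS, L-1 and COPE-8 are measured at t1, t2 and t5 only.
- **Size and retention.** "We plan to form two groups of 15 participants each". Table 1 sets Go at 60% or more for the "Proportion of CGs completing the *t*_5_ follow-up data collection".
- **Loss.** Progression criteria gives as one reason for its thresholds the "high probability of change in the informal care arrangement over the course of the study, which would result in participant exclusion". The Discussion expects some dropout and says that, once the care arrangement has changed, a CG's data are unusable from then on. Elsewhere it says: "as data will be collected via phone, we expect little missing data".
- **Divergence of the groups.** Both groups receive the same two-week on-site programme. They differ only in the digital phase and the refresher, so t1 and t2 precede any difference in treatment. CGs choose their own group.

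**The concern.** There are two issues.

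**Use of the data.** The repeated-measures and MANOVA procedures in SPSS drop a case with any missing value among the visits entered. A CG excluded after t3 would lose valid t1 to t3 data. This fits poorly with a plan that foresees exclusions and bars only later data. The expectation of little missing data rests on telephone collection, which helps with unanswered items but does nothing for CGs who have left the study. The estimate most exposed is the BSFC-s effect size, because it is carried forward to size the RCT. The planned allowance for small-sample overestimation does not address selective loss.

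**Meaning of the group effect.** In a mixed ANOVA the group main effect is the A-B difference averaged over all visits entered. Two of the five visits come before A and B are treated differently. Averaging them in shrinks a later difference. Because groups are self-chosen, it also brings in whatever difference existed at baseline.

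**Working it through.** The plan gives no precision or power calculation to reproduce; 30 is a compromise between two recommendations. The plan supplies N = 2 x 15, the 60% threshold, the visit schedule and the point at which A and B diverge. The SD, correlation and dropout pattern below are assumptions.

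**1. CGs entering a five-visit model.** 0.60 x 30 = 18, about 9 per group. This is a maximum at 60% retention, since a missed earlier visit removes a further CG.

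**2. Observations.** Assume even monotone dropout: 30, 27, 24, 21 and 18 CGs at t1 to t5. Available: 30 + 27 + 24 + 21 + 18 = 120 observations from 30 CGs. Complete-case: 18 x 5 = 90 observations from 18 CGs.

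**3. Precision of change from t1** (all CGs pooled, SD 5, exchangeable correlation r = 0.6).

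Complete-case SE, the same at every visit: SD x sqrt(2(1 - r)/18) = 5 x sqrt(0.8/18) = 1.054.

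Likelihood-based SE: sum the information over the dropout patterns (3, 3, 3 and 3 CGs last seen at t1, t2, t3 and t4, and 18 seen throughout), invert it, and take the variance of the t1 contrast.

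| Change from t1 to | Complete-case SE | Likelihood SE | Complete-case SE larger by |
|---|---|---|---|
| t2 | 1.054 | 0.852 | about 24% |
| t3 | 1.054 | 0.889 | about 19% |
| t4 | 1.054 | 0.930 | about 13% |
| t5 | 1.054 | 0.981 | about 8% (7.5%) |

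The penalty falls over time because fewer discarded CGs have data at the later visit. For t5 it is 7 to 9% for r from 0.8 down to 0.4.

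**4. Dilution of a group main effect.** Let A and B differ by 0 at t1 and t2 and by D at the later visits.

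- Five visits: (0 + 0 + D + D + D)/5 = 3/5 D = 0.60 D.
- BBCS, L-1 and COPE-8 (t1, t2, t5): (0 + 0 + D)/3 = 1/3 D.
- Contrast of the later visits against t1/t2: D - 0 = D.

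If self-selection produces a constant difference B at all visits, the five-visit main effect is B + 0.60 D, while the contrast against t1/t2 is (B + D) - B = D.

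**The case against.** The strongest reply is that the sentence is exploratory and open. Mixed ANOVA is only an example, no section states listwise deletion or which visits enter the model, and missing-data handling may be set in an analysis plan that is not shown. A t1 to t2 change can be computed from those two visits alone. The primary outcome is satisfaction, and no progression criterion uses the BSFC-s. These points stand and limit the weight of the concern. They do not remove it: the only models named are complete-case in their standard form, and they suit the plan's own account of exclusions less well than an available alternative.

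Four stronger readings are tempting and not supported:

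- **That 40% loss is forecast.** The 60% is a conservatively set Go threshold. The 18 of 30 is the lowest retention that still passes.
- **That precision suffers by about 30% throughout.** That figure holds only for the t1 to t2 change with no loss before t2. With even dropout it is 24% at t2 and shrinks to about 8% at t5.
- **That completers over-represent CGs who were doing well.** This needs dropout driven by high burden. The causes of exclusion that the Discussion names are the care receiver moving to a nursing home or dying. The direction and size of any bias are unknown.
- **That the MANOVA cannot be computed.** This would need all scales and all visits in one model, which no section plans. The abstract and the Inferential statistics section differ in wording, but the latter's example does not exclude MANOVA.

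The dilution is likewise conditional. The group effect is never defined as a five-visit average, and the group-by-time interaction, also planned, is not diluted this way. As an omnibus term over five visits, however, it does not isolate t3 to t5 against t1/t2.

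**Conclusion.** The concern holds in a limited form and is worth acting on. The named models, in standard SPSS form, would use as few as 18 of 30 CGs at the accepted retention and discard earlier data that the Discussion treats as usable. The loss of precision is moderate: about 24%, 19%, 13% and 8% in the SE of change from t1 at t2, t3, t4 and t5. These figures rest on SD 5, exchangeable correlation 0.6 and even dropout to 60%. No statement on bias can be made from the document. If the group effect is read as the main effect over all visits, a difference arising after t2 appears at 3/5 of its size (1/3 for the three-visit scales) and is mixed with self-selected baseline differences.

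**What to change.** - Name a linear mixed model for each scale (SPSS MIXED, REML) with group, categorical time and group-by-time, using all available visits.
- Report A-B differences as group-by-time contrasts of t3, t4 and t5 against the pre-divergence visits t1/t2, in place of a group main effect. For BBCS, L-1 and COPE-8 use t5 only.
- Align the abstract with this model.
- Report reasons for loss by group. The model assumes data missing at random, and loss through nursing-home entry or death of the care receiver may not meet that.

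The cost is a few sentences of wording and slightly more analysis work, with the same software and no new data.

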The aims of our pilot study are to (1) develop an outpatient preventive medical service for and in cooperation with working CGs and (2) explore CGs’ satisfaction with the service. Additionally, we aim to (3) clarify the effect of the service on individual outcomes and potential differences that depend on group assignment and (4) identify the need, feasibility, and acceptance of the outpatient preventive medical service and its different variants.

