## Methods/design

### Study design and setting

To test the CGs’ satisfaction with the developed outpatient preventive medical service, we will conduct a non-randomized prospective intervention study with two arms and a follow-up. Allocation will be based on the CGs’ preferences. Written informed consent will be obtained from every participant before the on-site treatment begins. The pilot study is coordinated by the Centre for Health Services Research in Medicine in Erlangen, Bavaria, Germany. The on-site treatment program will be based in community facilities and a health resort facility (Klinik Hohes Licht) in Oberstdorf, Bavaria, Germany. On-site treatment will take place from April to May 2026 and January 2027. The digital treatment program will be hosted on Cisco’s WebEx video platform, which uses end-to-end encryption (E2EE) and is in accordance with the EU General Data Protection Regulation (GDPR). Consent to use Cisco’s WebEx will be part of the written declaration of consent that participants will sign at the beginning of the intervention. The intervention will last from April 2026 to January 2027. Figure 1 presents an overview of the timeline for enrollment, intervention, and measurements. The pilot study protocol is reported in line with the SPIRIT 2025 guidelines [15, 29]. The SPIRIT 2025 checklist can be found as an additional file (see Additional file 1). The pilot study was registered at Deutsches Register Klinische Studien (DRKS), ID: DRKS00039025,01/22/2026 (https://www.drks.de/search/de/trial/DRKS00039025/details).

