#### Phase 2: execution of the outpatient medical service treatment

The outpatient preventive medical service will be split into three parts: a 2-week on-site outpatient treatment program in Oberstdorf, Bavaria, Germany in April and May 2026; a 9-month phase of digital support to implement the newly gained strategies and knowledge into everyday life; and a refresher treatment program in January 2027. To test whether more flexible and digital options could suit the CGs’ situation better, two different versions should be established with the same overall treatment hours but with differences regarding analogous treatment program time (group A: 2 weeks + 1 week, both on-site; group B: 2 weeks on-site + 2 days digital) and digital support (group A: 9 months of only a few sporadic occurrences of digital contact; group B: 9 months regular digital contact). To enable participants to plan time off work and arrange for caregiving for the CR, group allocation will be based on the CGs’ choice after they receive information about the schedule, dates, and procedures in both groups. Thus, no blinded group assignment can be provided. To detect possible confounders in group choice, participants will be asked about the reasons for choosing the respective group in qualitative interviews after the intervention.

The 2-week on-site treatment program will take place in rooms at the clinic (Klinik Hohes Licht), in community rooms, and outdoors in Oberstdorf, Bavaria, Germany during the day. Participants will spend the nights and weekends in accommodations organized by the local tourism board (Tourismus Oberstdorf). They will receive a financial allowance of 80€ per night as an incentive.

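### A BSFC-s effect size from a 30-person, self-selected pilot with no untreated arm is a biased and imprecise input for sizing the RCT, and the small-sample allowance does not repair it

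*Protocol article*

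**What the plan says.** - **Use of the estimate.** Under Inferential statistics, mixed ANOVAs are named as an example of the analyses that will estimate the effect size on BSFC-s, the planned RCT primary outcome. Then: "This estimate will inform the case numbers calculation for the following RCT, while accounting for an overestimation due to the small sample size". The same section explores pre-post changes, group effects and interactions with effect sizes and confidence intervals, but gives no rule for using an interval in the sizing.
- **Size.** Statistical analysis: "We plan to form two groups of 15 participants each". The reason given is a compromise between two cited recommendations, not a precision target.
- **Design.** Study design and setting: "Allocation will be based on the CGs’ preferences". Under Phase 2, group allocation follows the caregivers' "choice after they receive information about the schedule, dates, and procedures in both groups", and "Thus, no blinded group assignment can be provided". Both groups get the same two-week on-site programme; they differ in digital support and in the refresher. There is no untreated, waiting-list or usual-care arm.
- **Entry and exit.** Entry requires a BSFC-s score of 5-25 (Participant characteristics). Caregivers whose care arrangement changes leave the data (Discussion). Table 1 accepts 60% completion at t5.
- **Claims.** Aim 3 in the Background is to "clarify the effect of the service on individual outcomes and potential differences that depend on group assignment". Inferential statistics adds: "A responder analysis will be conducted to determine which CGs benefit the most from the interventions".

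**The concern.** A sample size calculation needs a difference that the trial ought to detect, plus nuisance quantities such as the SD. The protocol plans to draw on the pilot for the first of these, where the pilot is weakest. The article does not state the RCT comparator, but neither possibility rescues the estimate.

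- **RCT against no service or usual care.** The pilot has no such arm, so only pre-post change is available. That change also contains natural course, expectation, regression to the mean (entry is judged on the outcome scale itself) and the selection of those who complete.
- **RCT of version A against version B.** The pilot makes this contrast, but in groups that chose themselves. The only stated handling is to ask, after the intervention, why each group was chosen.

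The stated safeguard concerns overestimation from a small sample. It does not supply a control, undo self-selection or narrow an interval. At stake is an RCT that is too small, or needlessly large, in people who are already burdened. The responder sentence has the same gap: without a control, individual change is not individual benefit.

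**Working it through.** The planned 15 per group comes without alpha, power, SD or effect size, so there is no figure to reproduce. The check asks what an estimate from this pilot could support.

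**Inputs from the protocol.** 15 per group, 30 in total; 60% retention, so 0.60 x 30 = 18, or 9 per group if losses are even; BSFC-s entry range 5-25.

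**Assumptions, not in the protocol.** RCT with two-sided 5%, 80% power and 1:1 allocation; the illustrative values of d; for step 6, SD 5, mean 15, a drop of at least 3 points as response, and the reliabilities.

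**1. Precision of A-B at one time point** (noncentral-t 95% CI, observed d = 0.5)
- 15 per group: -0.23 to 1.22
- 9 per group: -0.45 to 1.43

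**2. RCT size implied**, n per arm = 2(1.960 + 0.842)²/d² = 15.70/d² (normal approximation)
- d = 0.3: 175
- d = 0.5: 63
- d = 1.22: 11
- at the lower limit of either interval in step 1, no size exists

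**3. Pooled pre-post change**, observed dz = 0.5
- n = 30: 0.12 to 0.88. Read as if it were the RCT effect, that is 21 to 1,165 per arm (unrounded limits 0.876 and 0.116).
- n = 18: about 0.00 to 0.98

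**4. What repeated measures gain.** Approximate baseline-adjusted A-B interval at 15 per group: 0.5 ± 2.052 x sqrt[(2/15)(1 - r²)].
- r = 0.6: 0.5 ± 0.60, or -0.10 to 1.10
- r = 0.8: 0.5 ± 0.45, or 0.05 to 0.95

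These are narrower but still wide, and they centre on the same confounded quantity.

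**5. What a small-sample correction does.** The method behind the allowance is not described. If it is the Hedges factor 1 - 3/(4df - 1), it is 0.973 at 28 df and 0.952 at 16 df. Then d = 0.5 becomes 0.486, and the RCT goes from 63 to 67 per arm. In a simulation of 200,000 pilots (true d = 0.5, 15 per arm, Hedges-corrected, no bias at all), 9% gave an estimate at or below zero. Among the rest, the RCT size ran from 16 to 620 per arm (10th to 90th percentile), and 53% of those RCTs had true power below 80%.

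**6. Responders with no true effect.** Two scores per person share a true value and have independent error; the first is limited to 5-25.
- reliability 0.6: 35% respond above the median baseline, 14% below
- reliability 0.8: 23% against 11%

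High-baseline caregivers therefore look like responders through fluctuation alone. In the same simulation the entry window moved the mean change by no more than about 0.3 points, in either direction, at population means of 12 to 18. Regression to the mean is thus mainly a problem for the responder comparison. Its part in the mean change could be larger if caregivers enrol when burden is unusually high, which cannot be quantified here.

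**7. What the pilot can supply.** Factor for the upper 80% confidence limit of an SD: sqrt(df/chi-square at 0.20).
- 28 df: sqrt(28/21.59) = 1.14; squared, n x 1.30
- 16 df: sqrt(16/11.15) = 1.20; squared, n x 1.43

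**The case against.** Several stronger readings are tempting, and the protocol does not support them.

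- **That the pilot estimate alone will fix the RCT size.** The wording is that it will inform the calculation, with an allowance for overestimation, and confidence intervals will be reported.
- **That the pilot contrast cannot be what the RCT tests.** The comparator is never given. Phase 2 sets up the two versions to see whether flexible, digital options suit caregivers better, so an A-against-B trial is possible. What can be said is that the estimate is biased under either comparator.
- **That time away from home contaminates the pre-post change.** The Background presents delivery away from home as beneficial, so it is an intended ingredient of the service.
- **That the interval always runs from no effect to a very large one.** That is so for the single-time-point A-B contrast at d = 0.5. Steps 3 and 4 show intervals that exclude zero.

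It is also fair to say that the pilot's primary outcome is satisfaction, that no criterion in Table 1 uses BSFC-s or responder status, and that the Abstract calls the quantitative analysis descriptive and exploratory. The harm therefore falls on a later trial that will need its own justification.

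These points limit the wording and the severity. They do not meet the core: no correction for sample size supplies a missing control arm or removes free choice of group.

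**Conclusion.** The point holds and should be fixed, but it does not threaten the pilot's own conduct or its progression decision. The bias follows from the design as written and needs no assumed number; its size cannot be calculated from the protocol. The imprecision rests on the stated group sizes and on illustrative effect sizes; the RCT sizes also assume two-sided 5% and 80% power. The responder percentages only illustrate the mechanism under an assumed SD, mean, cut-off and reliability, since the article defines no responder. The 3-5% shrinkage holds only if the Hedges factor is meant; the cited method may shrink more, but that would still not address the bias.

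**What to change.** 1. **Replace the sizing sentence** under Inferential statistics, for example: *The RCT will be sized on a BSFC-s difference specified in advance as worthwhile. The pilot will supply the BSFC-s standard deviation (using a conservative upper confidence limit), the within-person correlation and retention; an allowance for delivery in groups will be added.* The 80% limit is one convention among several.
2. **Report pilot BSFC-s changes descriptively**, by group and pooled, with confidence intervals.
3. **Reword aim 3** to describing change in individual outcomes by group.
4. **Reword the responder analysis** as a descriptive account of individual trajectories, with no claim about who benefits.

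Items 2 to 4 are changes of wording. Item 1 costs a little more. The worthwhile difference must be justified or elicited, and the development interviews and focus group already took place in February 2026, so this is a short extra step. With the 80% limit, the RCT would be about 30% (28 df) to 43% (16 df) larger than with the point SD.

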#### Primary outcome measure

We will use the participants’ overall satisfaction with the outpatient preventive medical service as the primary outcome measure after each part of the intervention and at the follow-up (*t*_2_, *t*_3_, *t*_4_, *t*_5_). Satisfaction will be measured quantitatively using the German version of the Client Satisfaction Questionnaire [4], an economical, valid, and reliable scale [35, 61] to depict the overall level of patient satisfaction with healthcare services. Participants will answer 8 items on a 4-point Likert scale. Sum scores will range from 8 to 32, with higher scores indicating higher satisfaction. A sum score of 23 or higher indicates satisfaction with the program [35]. Additionally, satisfaction will be assessed via qualitative interviews at *t*_2_ and *t*_4_. For more information regarding the qualitative interviews, see the Qualitative Data section.

Participants will rate their satisfaction with the individual activities they attended both on-site and online in form of feedback-oriented visual analog scales [21].

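### With groups formed by preference, a group main effect averaged over all visits is a poor A-B estimate: it absorbs a baseline gap and dilutes any variant effect

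*Protocol article*

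**What the plan says.** The section on study design states: "Allocation will be based on the CGs’ preferences". The description of Phase 2 adds that "group allocation will be based on the CGs’ choice after they receive information about the schedule, dates, and procedures in both groups". The third aim, in the Background, is to "clarify the effect of the service on individual outcomes and potential differences that depend on group assignment".

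The section on inferential statistics gives mixed ANOVAs as an example of the models for BSFC-s, the intended primary outcome of the later RCT. It then lists pre-post changes and says that "group effects and group-by-time interactions will be explored using effect sizes and confidence intervals". It does not say which visits enter the group effect.

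For BSFC-s and the five other scales measured at t1 to t5 (PSS-10, PHQ-9, PHQ-15, MBI, TILS), the protocol says "we will assess sum scores at baseline, after each part of the intervention, and at follow-up". BBCS, L-1 and COPE-8 are measured at t1, t2 and t5.

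The protocol foresees confounding. Its stated response is in the description of Phase 2: "To detect possible confounders in group choice, participants will be asked about the reasons for choosing the respective group in qualitative interviews after the intervention".

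**The concern.** The abstract says that both groups take part in the same on-site treatment and differ in the intensity of digital support and the location of the refresher. At t1 and t2, therefore, no difference between variants can yet exist; only differences between the people who chose them can. A group main effect over all visits gives those two visits the same weight as t3, t4 and t5. If caregivers who choose one variant start with a higher burden, much or all of that gap appears as a group effect, and any real variant effect shrinks.

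Aim 3 asks about differences by group, and the pilot is to inform an RCT. A contrast that mainly shows who chose which variant could be read as evidence on the variants themselves. The interview question about reasons for choice helps interpretation but does not change an effect size or its interval.

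**Working it through.** **Inputs from the protocol.** 15 per group; five visits for BSFC-s and similar scales; on-site treatment common to both groups, so A and B diverge only after t2. The sample size is a compromise between recommendations, with no power calculation, so there is no planned figure to reproduce.

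**Assumptions, not in the documents.** Gap at t1 of d = 0.5 SD; equal correlation r = 0.6 between all visits; no true A-B difference; main effect taken over all five visits. Two cases: the gap is stable (d at every visit), or it regresses to r × d = 0.3 SD after t1.

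**Spurious A-B difference in SD units**

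| Estimate | Gap stable | Gap regresses |
|---|---|---|
| Five-visit group main effect | 0.50 | (0.5 + 4 × 0.3)/5 = 0.34 |
| Change from t1 to t5 | 0.5 − 0.5 = 0.00 | 0.3 − 0.5 = −0.20 |
| t5 adjusted for t1 (slope r) | 0.5 − 0.6 × 0.5 = 0.20 | 0.3 − 0.6 × 0.5 = 0.00 |
| t5 adjusted for t1 and t2 (slope r/(1 + r) = 0.375 each) | 0.5 − 0.375 × (0.5 + 0.5) = 0.125 | 0.3 − 0.375 × (0.5 + 0.3) = 0.00 |

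**Dilution.** A constant variant effect present at t3, t4 and t5 contributes 3/5 = 60% of its size to the five-visit main effect. For the scales measured at t1, t2 and t5 the share is 1/3.

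**If fewer visits are used.** Over t2 to t5 the main effect still carries 0.50 SD (stable) or 0.30 SD (regressing), and dilution is 3/4. Over t3 to t5 the dilution disappears but the same gap remains.

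**Other correlations.** With a stable gap, the bias after adjustment for t1 and t2 is 0.5 × (1 − 2r/(1 + r)): 0.17 SD at r = 0.5 and 0.09 SD at r = 0.7. In a simulation of 5,000 pilots at r = 0.7, a two-sided 5% test of the main effect rejected in 33% (stable) and 21% (regressing). The t1-to-t5 change contrast rejected in 5% and 8%.

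**How likely is such a gap?** The standard error of a baseline difference is sqrt(2/15) = 0.365 SD. Chance alone therefore gives a gap beyond 0.5 SD in either direction with probability 2 × (1 − Φ(0.5/0.365)) = 0.17. Self-selection can add to this.

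**Precision with equal groups, r = 0.6.** The standard error of the change contrast is sqrt(2 × 0.4 × 2/15) = 0.33 SD. Adjusted for t1 and t2, the residual variance is 1 − 2 × 0.36/1.6 = 0.55, so the standard error is sqrt(0.55 × 2/15) = 0.27 SD, or about 0.28 SD once estimation of the two slopes is allowed for (simulated).

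**The case against.** A reader might infer that all planned A-B estimates ignore the starting value. The protocol does not support that. Pre-post changes and group-by-time contrasts subtract t1, so a stable gap cancels; only regression to the mean or different trends can bias them.

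A reader might also infer that baseline adjustment is the right analysis and change the wrong one. The table shows otherwise: with a stable gap, change is unbiased and adjustment leaves 0.125 to 0.20 SD; with a regressing gap the ranking reverses. The protocol gives no basis for deciding which case applies, and choice may follow schedule and dates more than burden.

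It is also fair to say that naming mixed ANOVA as an example excludes no covariate, and that covariate lists are commonly left to an analysis plan, which is not shown. An unlisted covariate is therefore not the complaint. The protocol does acknowledge confounding, and it integrates interview findings at interpretation.

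The stakes are limited. The contrasts are labelled exploratory, and none of the criteria in Table 1 is an A-B comparison. With 15 per group the 95% half-width for a simple two-group difference is 2.05 × 0.365 = 0.75 SD, so a bias of 0.34 to 0.50 SD lies inside the noise of one pilot. The primary outcome, satisfaction, is used "as the primary outcome measure after each part of the intervention and at the follow-up", so it has no t1 value and lies outside this point.

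All of this stands and narrows the point. It does not rescue the group main effect, which the protocol names as an A-B estimate and which a stable gap enters in full.

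**Conclusion.** The point holds for one named estimate. Under preference allocation, a group main effect over all visits does not answer aim 3. For an assumed gap of 0.5 SD and r = 0.6 it shows 0.34 to 0.50 SD with no true difference, and it reports 60% of a constant effect that begins at t3. The size scales with the assumed gap; the documents give no SD or correlation to narrow it. The 60% follows from the visit schedule if all five visits are used.

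The change and group-by-time contrasts are sound against a stable gap, and adjustment is a useful companion to them, not a replacement. No estimate from this design removes unmeasured preference effects. Severity is minor.

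**What to change.** In the section on inferential statistics:

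- State that the all-visit group main effect is not used as the A-B difference.
- For BSFC-s and the other t1-to-t5 scales, report the A-B contrast at t3, t4 and t5 as the planned change from t1 and, beside it, as an estimate adjusted for the caregiver's own t1 and t2 scores. If one group is postponed from April to November, as the Discussion allows, adjust for t1 only, because t2 would then fall in different seasons.
- For BBCS, L-1 and COPE-8, do the same at t5.
- Show t1 values by group, and state that neither estimate removes unmeasured preference effects, so an A-B difference is not read as a variant effect alone.

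No new data are needed. The cost is one or two residual degrees of freedom per model and more exploratory estimates to present: 6 scales × 3 visits + 3 scales × 1 visit = 21 adjusted contrasts, before subscales. A larger covariate set is not advised: at the 60% retention benchmark only 0.6 × 30 = 18 caregivers would remain.
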